#### **6.3.6 Further supplementary analyses**

Demographic and other baseline data will be summarised descriptively by randomized arm in the FAS. Continuous data will be summarised by arithmetic mean, standard deviation, minimum, 25% quantile, median, 75% quantile, maximum, and the number of complete and missing observations. If appropriate, continuous variables can also be presented in categories. Categorical data will be summarised by the total number of patients in each category and the number of missing values. Caregivers frequencies are displayed as valid % (number of patients divided by the number of patients with non-missing values).

All data items needed for reporting of trial results in compliance with the CONSORT (Schulz, Altman, & Moher, 2010) and CONSORT-EHEALTH (Eysenbach & CONSORT-EHEALTH Group, 2011) statements will be evaluated.

## **6.4 Qualitative methods**

Based in the interview transcripts, a qualitative content analysis is carried out. The focus of the qualitative analysis is on the subjective perception of the interviewed person. Depending on the research question, an appropriate method within the grounded theory framework is selected. Our research group is experienced in both constructivist grounded theory analyses (Charmaz, 1996, 2006) and core sentence (“Kernsatz”) analyses (Burkhardt, 2016; Leithäuser & Volmerg, 1988). For the messages between participants and psychologist from the individual support condition, an appropriate form of qualitative or quantitative content analysis is chosen for each research question.

## **7 Methods: Monitoring**

### **7.1 Data Monitoring**

Following the guideline on data monitoring committees (European Medicines Agency [EMA]) Committee for Medicinal Products for Human Use [CHMP], 2005), neither a data monitoring committee nor interim analyses are considered necessary for this study, given the non-patient participants, short intervention as well as study time and low risk of harm expected from the intervention. The lead investigator will monitor the progress of the study with regard to the safety-relevant development as detailed in section 7.2.

### **7.2 Harms**

The objective of this online-coach is to effect a positive change of caregivers' psychological burden and everyday life. Each change includes a risk for undesirable side effects. Side effects can be impacts on everyday life, interpersonal relationships (e.g. conflicts due to caregivers setting more boundaries towards the patients) and increased awareness of the burdens. Moreover, a temporary burden through the active analysis of actual stress factors is possible. For risk assessment (serious) adverse events ((S)AE) will be defined ahead of the study and recorded during the course of

studies. (Serious) adverse events are the occurrence or deterioration of psychiatric symptoms of the caregiver or the depressive person.

In case of a (S)AE there is an emergency button on the website of the online program, where the participant can find information and contacts of emergencies services and will be asked to contact them.

If (S)AE occur in the psychological message system contact or if participants contact a study member in case of an (S)AE, the lead investigator will be informed of the (S)AE immediately and will decide on the further procedure (e.g. study exclusion and outpatient or inpatient treatment recommendations).

For the following reasons, the intervention will be ceased in subjects of the study:

- Revocation of the subject's declaration of consent
- If, in the opinion of the lead investigator, further participation in the study would have harmful effects on the subject or the depressive person
- In case of new exclusion criteria
- If the emotional burden for the subject is too serious to cope with it himself, and intensive (professional) support is needed

Exclusion is decided by the lead investigators, in case of fulfilling one of the mentioned criteria. The reason for exclusion will be recorded. If needed, excluded subjects will be supported in searching further consulting or treatment. Also, if the subject revokes the informed consent, the subsequent reason will be recorded.

The lead investigator will monitor the progress of the study with regard to safety-relevant development. The lead investigator will discontinue the study, if:

- the cost-benefit ratio for the caregiver or the depressive ill person changes significantly
- there are indications, that the security of the caregiver or the depressive ill person is no longer guaranteed
- the continuation of the study is no longer justified by ethical or medical reasons
- the questions of the study can be clearly answered by results of another study

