## **8 Ethics and dissemination**

### **8.1 Research ethics approval**

Through working on the online self-help program and the messaging system the participating caregivers are expected to get better and more confident handling with the diagnosis depression and with the interpersonal interaction with the depressed person. Information and help is given, which applies in everyday life and the relationship. Also, the caregiver's self-care is strengthened. Concerning the co-participating depressive person, it is expected, that through the caregiver's participation everyday interaction is getting more useful and less confrontational. Hence, it results a relief for the depressed person. As the online self-help program is a supportive and informing online-intervention, we expect that participation has a positive impact on everyday life and on the mental burden of the participating caregivers. In certain circumstances it may happen, that some subjects do just less or not benefit from the online-intervention. Since the results of this study help to better understand the burden of caregivers of depressive persons, all subjects help to improve possibilities for supporting caregivers of depressive persons.

The objective of this online self-help program is to effect a positive change of caregiver's psychological burden and everyday life. Each change includes a risk for undesirable side effects. Side effects can be impacts on everyday life, interpersonal relationships (e.g. conflicts due to more delimitation) and experiencing of the burden. Moreover, a temporary burden through the active analysis of actual stress factors is possible. Subjects will be informed about all potential side effects by the informed consent.

During the whole study period, subjects can, if required (e.g. in case of a serious event), call a study member – or out of working hours – the doctor of the university clinic of psychiatry and psychotherapy, Freiburg.

Subjects will be informed about the study and all measures within the study. The participant consent (double opt-in) must be obtained before any trial-specific tests. Participation can be ceased at any time without necessarily giving any reason and without any loss of benefits in case of a (further) treatment at the university clinic Freiburg (independence of study and treatment).

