## **8.7 Ancillary and post-trial care**

As detailed in section 7.2, only mild and transient harms are plausibly expected from the planned interventions. Participants who encounter serious adverse events during the course of the study will be assisted in finding appropriate treatment where necessary.

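### The (S)AE definition in Section 7.2 covers only psychiatric symptoms, so it does not cover all the side effects that Sections 7.2 and 8.1 expect, and it does not separate AE from SAE

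*Protocol*

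**What the plan says.** Section 7.2 of the protocol opens with the risks that the sponsor foresees: "Side effects can be impacts on everyday life, interpersonal relationships (e.g. conflicts due to caregivers setting more boundaries towards the patients) and increased awareness" (here, awareness of burden). It adds: "Moreover, a temporary burden through the active analysis of actual stress factors is possible". Section 8.1 repeats the list, in the words "Side effects can be impacts on everyday life, interpersonal relationships (e.g. conflicts due to more delimitation) and experiencing of the burden", again mentions a temporary burden, and states that the consent information tells participants about all potential side effects.

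Section 7.2 then turns to what is recorded: "For risk assessment (serious) adverse events ((S)AE) will be defined ahead of the study and recorded during the course of" the study. The next sentence supplies the definition: "Serious) adverse events are the occurrence or deterioration of psychiatric symptoms of the caregiver or the depressive person". It serves AE and SAE alike, and so does the notification procedure that follows.

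Section 8.7 uses the serious category on its own: "Participants who encounter serious adverse events during the course of the study will be assisted in finding appropriate treatment where necessary".

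Sections 4.5 and 6.1.1 say that all caregivers are asked about adverse events at T2 and again at T3. The schedule in Section 6.1.2 lists an adverse events questionnaire at both visits. Its items are not described.

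**The concern.** The harms that the protocol expects and the harms that it defines for recording are two different lists. A caregiver who works through the relationship and self-care modules and then has marked conflict with the depressed person, without psychiatric symptoms in either of them, has had the protocol's own example of a side effect. Under Section 7.2 that caregiver has had no (S)AE.

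If the adverse event comparison of IND, AUT and TAU follows the definition as written, it omits relationship and everyday-life harms that participants are told about at consent. A statement that the arms did not differ in adverse events would then say nothing about those harms.

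Section 7.2 carries particular weight here. Section 7.1 provides no data monitoring committee and refers safety monitoring to 7.2, and Section 7.3 provides no external audit. The lead investigator is asked to judge whether the balance of benefit and cost changes for caregiver or depressed person, using event data whose definition leaves out part of the expected cost.

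The shared definition is a second, smaller matter. Without a criterion for seriousness, the same worsening of symptoms could be classed as AE or SAE, although Section 8.7 attaches an action to the serious class alone.

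**Working it through.** No sample size, power or event figure enters this point, so there is nothing to recompute. The check sets the passages side by side.

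**Step 1. Named side effects against the definition.**

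| Side effect named in 7.2 and 8.1 | Within the (S)AE definition in 7.2? |
|---|---|
| Impacts on everyday life | No |
| Effects on relationships, with conflict as the example | No |
| Greater awareness or experience of burden | Only if it shows as psychiatric symptoms |
| Temporary burden from working on stressors | Only if it shows as psychiatric symptoms |

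Two of the four are outside and two are inside conditionally. A conflict that also brings psychiatric symptoms would be captured through the symptoms.

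**Step 2. Is the definition open or closed?** The sentence says what (serious) adverse events are. It contains no wording that marks psychiatric symptoms as one example among others, and no other section gives a further definition.

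**Step 3. Is there another route that records these effects as harm events in all three arms?**

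- IEQ-EU, FFB and K-10 (Sections 4.4 and 6.1.2) go to every caregiver, but as outcome scales. A difference in mean scores does not count caregivers with an event.
- Interviews (Section 6.1.5) cover selected individuals only.
- Reasons for ending participation (Section 6.1.4) and for exclusion (Section 7.2) concern only those who leave.
- Events that surface in the psychologist's messages can do so only in IND. Section 4.5 states that AUT caregivers cannot reply to their messages, and TAU has no message support.
- Contact with a study member is open to all arms but relies on the participant to report.

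The T2/T3 questionnaire is therefore the only systematic collection of adverse events in all three arms, and the only definition it can rest on in this document is the one in Section 7.2.

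**Step 4. Separation of AE from SAE.** Definitions that apply to SAE alone: none. Seriousness criteria anywhere in the protocol: none. Places where an action depends on the serious class alone: one, Section 8.7.

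**The case against.** The strongest reply is that the record depends on the questionnaire, not on one sentence. Section 7.2 says that (S)AEs will be defined ahead of the study, which may point to a fuller definition elsewhere, and the questionnaire may well ask about conflict or everyday impairment. This stands as a limit. A reader might infer that none of the named harms would be captured, or that the trial could not produce a count of serious events. The document does not show either, because the questionnaire items are not in it. It does not rescue the text, however, since the sentence that follows the announcement gives a definition without any opening for other events.

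A second reply is that keeping side effects apart from (S)AEs may be deliberate. Setting boundaries is close to the program's self-care aim, some conflict may follow from the program working, and Section 8.7 expects only mild and transient harms. That is a fair reason not to call every conflict an adverse event. It is no reason to leave such effects without any recording category.

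A third reply is that burden and interaction are measured in every arm with a TAU comparison, and that the additional K-10 items touch on performance and medical visits. A systematic worsening in one arm could show in these scores. That is true and lowers the risk of a misleading safety conclusion, but a mean can improve while a minority has a harmful event.

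Finally, participant protection does not hang on the definition. The grounds in Section 7.2 for ceasing the intervention include harmful effects and excessive emotional burden without requiring psychiatric symptoms, and every reported (S)AE goes to the lead investigator. This stands: the weakness lies in ascertainment and reporting, not in escalation.

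**Conclusion.** The point holds in a limited form, with moderate confidence. The (S)AE definition in Section 7.2 does not cover two of the four side effects that Sections 7.2 and 8.1 name, covers the other two only when they appear as psychiatric symptoms, and is not supplemented by any other route that records them as harm events in all arms. The missing split between AE and SAE is mainly a matter of clarification.

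The conclusion assumes that Section 7.2 is the working definition for the T2/T3 questionnaire. If the questionnaire already asks about the named effects, what remains is a discrepancy between documents.

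No number of missed events can be given, because the protocol states no rate for these effects. A reader might look to the survey figures in Section 3.1 on partnership problems and separation. Those describe the effect of depression on couples and have no trial time horizon. They are not rates of harm from the intervention, and many caregivers in this trial are not partners. The primary analysis and the efficacy conclusions are unaffected.

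**What to change.** Reconcile Sections 7.2, 8.1 and 8.7 with the T2/T3 adverse events questionnaire:

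- State that each side effect named in Sections 7.2 and 8.1 is asked of all caregivers at T2 and T3 and recorded, either as an AE or in a separate side-effect category. The second option answers the worry that ordinary boundary-setting would be labelled an adverse event.
- State a criterion that separates AE from SAE, so that the class to which Section 8.7 refers can be identified. Its content is for the sponsor to decide.
- Report counts by type and randomised arm, with AE and SAE shown separately.

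The cost is some wording and, if they are not already there, a few items in an online questionnaire that all caregivers receive. The form becomes slightly longer and more events will be reported. Since some conflict and burden will occur without the program, the counts should be read against TAU.

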### **3.2 Objectives and estimand**

The objective of the research project is to increase the efficacy of an online self-help program for caregivers of depressed persons by developing and implementing individualized vs automated support via secure e-mail messages. Within this evaluation study the following primary research question will be addressed: Which impact has the four-week usage of the online self-help program with individualized or automated e-mail support vs treatment as usual on the risk of mental diseases in caregivers? In order to achieve this, we strive to determine if a treatment policy assigning caregivers of depressed persons to an individualised or automated online self-help intervention reduces the caregiver's unspecific mental distress compared to assignment to treatment as usual (TAU), as measured by the change of the K-10 score from baseline to four weeks after randomisation (post-measurement minus baseline). The change in mental distress is considered relevant regardless of whether or not the caregiver adheres to or discontinues the assigned treatment. Treatment arms should be compared with respect to the difference in means of the change in K-10 score.

---

 The self-help program evaluated in this study addresses relatives as well as close friends, colleagues, roommates etc., who give support to a depressed person and are affected by the depressive disorder. In the following, they will be referred to summarily as caregivers.

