### **6.1.4 Data collection quality**

To improve data completeness the participants will get repeated E-Mail reminders, if they don't fill in the questionnaires at T1, T2 or T3. For completing all measurements, the caregivers get a compensation in the form of a 30€ voucher (10€ for each measurement point, to be traded in at a large number of services).

If participants choose to end participation in the study, they will be asked to provide their reasons. Participants no longer interested in the intervention will nonetheless be asked to complete all measurements.

To promote data quality, data will be monitored during data collection. Data monitoring will consist of blinded reviews of the data for programming errors (e. g., data ranges different than expected) as well as for missing data. If problems are detected, corresponding steps will be taken (e. g., additional efforts to reach participants for each measurement if a large proportion of data is found to be missing).

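### Section 7.2 does not separate stopping the intervention from exclusion from the study, so T2 scores of caregivers stopped by the investigator are not secured

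*Protocol*

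**What the plan says.** Section 7.2 of the protocol defines an adverse event as the occurrence or "deterioration of psychiatric symptoms of the caregiver or the depressive person". When one comes to light, "the lead investigator will be informed of the (S)AE immediately and will decide on the further procedure (e.g. study exclusion"; the same parenthesis also names treatment recommendations. A list follows, opened by "For the following reasons, the intervention will be ceased in subjects of the study". It contains revoked consent, harm expected from further study participation, newly met exclusion criteria, and an emotional burden that needs professional support. Directly after the list comes "Exclusion is decided by the lead investigators, in case of fulfilling one of the mentioned criteria". For excluded caregivers the section provides a recorded reason and help in finding care. It does not mention later questionnaires.

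Two routes bring an event to the lead investigator: the psychologist message system, or "or if participants contact a study member in case of an (S)AE". Section 8.1 repeats that "subjects can, if required (e.g. in case of a serious event), call a study member".

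On measurement after a stop, section 6.1.4 has one sentence: "Participants no longer interested in the intervention will nonetheless be asked to complete all measurements".

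The estimand in section 3.2 is treatment policy: "The change in mental distress is considered relevant regardless of whether or not the caregiver adheres to or discontinues the assigned treatment". Section 6.3.2 analyses all randomized caregivers in their assigned arm. It fills missing T2 values by multiple imputation within arm, on the assumption that caregivers with missing outcomes resemble observed caregivers with similar baseline data and adherence.

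**The concern.** A treatment-policy estimand needs the T2 score of every randomized caregiver, above all of those whose treatment was stopped. Section 7.2 uses the language of stopping treatment and of leaving the study for the same criteria, and the retention sentence in 6.1.4 describes a caregiver's own choice, not an investigator's decision. A study team could follow 7.2 to the letter and send no further questionnaires to an excluded caregiver.

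Such missing scores would be related to the outcome. The K-10 is used as an indicator of the risk of mental illness (4.4). Newly met exclusion criteria are a listed reason, and the caregiver exclusion criterion in 4.2.1 is any mental disorder. A caregiver who falls ill during the four weeks thus meets an exclusion reason through the kind of event the trial wants to capture. Imputation from caregivers who stayed would tend to give such a person too good a value. If one arm loses more such caregivers than another, the comparison shifts in favour of the arm that loses more. The SAP can choose how to impute, but it cannot recover a score that was never collected.

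**Working it through.** **The plan's own figures.** Inputs: SD of change 6.2 and T0–T2 correlation 0.5 (6.3.2); 400:400:200 evaluable (4.6).

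- SE(IND−AUT) = 6.2 × √(2/400) = 0.438. SE(IND−TAU) = 6.2 × √(1/400 + 1/200) = 0.537.
- Power = P(Z > 1.96 − effect/SE). For d = 0.2 (1.24 points) this is 81%; for d = 0.3 (1.86 points) it is 93%. Both match section 4.6.
- The planned model adjusts for baseline K-10, so the residual SD is 6.2 × √(1 − 0.5²) = 5.37. The SEs become 0.380 (IND−AUT) and 0.465 (IND−TAU), and power becomes about 90% and 98%.

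**Size of a possible bias.** The protocol gives no exclusion rate, so every input here is an assumption. Let f be the net excess of excluded and unmeasured caregivers in one arm, and g the mean gap between their true and imputed T2 score. Then bias = f × g.

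The gap comes from a simulation of 2,000,000 caregivers with normal T0, T1 and T2 scores, SD 6.2, T0–T2 correlation 0.5, and T1 correlations of 0.6 or 0.7. T2 of the excluded is imputed by regression on T0 and T1 among the retained.

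- Upper case, all exclusions from the worst tenth of K-10 changes: g = 5.6 to 7.3 points.
- Middle case, half from the worst tenth and half at random: g about half of that. This could arise because half the stops concern the depressed person.
- Zero case, questionnaires continue after the stop: bias 0 if the scores are obtained.

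| f | Caregivers of 500 | Bias, middle to upper case (points) | False rejection IND=TAU, adjusted SE | False rejection IND=AUT, adjusted SE |
|---|---|---|---|---|
| 1% | 5 | 0.03 to 0.07 | 5.0% to 5.2% | 5.1% to 5.4% |
| 2% | 10 | 0.06 to 0.14 | 5.2% to 6.0% | 5.3% to 6.5% |
| 5% | 25 | 0.15 to 0.37 | 6.1% to 12.3% | 6.7% to 16.1% |

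False rejection = Φ(−1.96 + bias/SE) + Φ(−1.96 − bias/SE). Example, f = 2%, IND=AUT: 0.137/0.380 = 0.36, giving Φ(−1.60) + Φ(−2.32) = 6.5%. With the unadjusted SEs the upper values at 5% are 10.5% and 13.3%. A bias of 0.15 to 0.37 points is 12% to 30% of the 1.24-point difference.

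**Opposite direction.** If the comparator loses more, the bias works against IND. At 2% (−0.057 to −0.137 points), under the adjusted model:

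- IND=AUT at d = 0.2: P(Z > 1.96 − 1.103/0.380) = 83% at worst and 88% at best.
- IND=TAU at d = 0.3: P(Z > 1.96 − 1.723/0.465) = 96% at worst and 97% at best.

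Both stay above the stated 81% and 93%. At 5% in the worst case, IND=AUT would fall to P(Z > 1.96 − 0.874/0.380) = 63%, so this reassurance holds for 1% to 2% only.

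**The case against.** Section 7.2 can be read as stopping treatment only. Its list opens with the intervention, nothing says that questionnaires end, and the T2 schedule and the reminders are not limited to adherent caregivers. This stands, and it is why the range starts at a bias of zero. It does not settle the matter, because the section also speaks of study exclusion and of harm from further study participation. In TAU the intervention is a two-page leaflet, so there is little to stop other than participation.

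Exclusion is discretionary, and harms are expected to be mild and transient (8.7). This also stands. In the upper case, a 5% excess means that 25 of the 50 worst-changing caregivers in a 500-person arm are detected, excluded and unmeasured, over and above losses in the comparator. Nothing in the protocol makes that likely.

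The analysis gives partial cover. Imputation may use post-baseline information, and K-10 is collected at T1. The sensitivity analysis in 6.3.3 gives IND and AUT caregivers who withdraw TAU-like values. This removes an advantage from within-arm imputation but does not reproduce a deterioration.

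The remedy will not recover every score. Revoked consent ends collection, some caregivers will not answer, and the harm reason overlaps with the proposed exception.

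A reader might infer that the protocol drops deteriorated caregivers from the analysis. It does not: 6.3.2 keeps all randomized caregivers. A reader might also infer a bias in favour of IND, because only IND has two-way messages with a psychologist (4.5). But caregivers in every arm can contact a study member (7.2, 8.1), so the difference in detection is one of degree and its net direction is uncertain.

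**Conclusion.** The point holds as an unclear rule with a cheap remedy, and it is minor. Section 7.2 merges stopping treatment with leaving the study, and no sentence secures T2 for caregivers stopped by the investigator. On the reading that exclusion ends measurement, this conflicts with sections 3.2 and 6.3.2.

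The size is unknown and probably small: 0 to 0.14 points at a net excess of 1% to 2%, with false rejection at most about 6.5% and no power below the stated values under the baseline-adjusted model. Only an excess of about 5% would be material. These figures rest on assumed exclusion rates, an assumed link between exclusion and the worst changes, and assumed T1 correlations. The documents do not support a claim that the trial will be biased, or in which direction.

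**What to change.** In section 7.2, replace *study exclusion* with *stop of the assigned intervention*, and *Exclusion is decided* with *The stop is decided*. Add to 7.2, and extend the sentence in 6.1.4 accordingly: caregivers whose intervention is stopped by the investigator are still asked to complete T1, T2 and T3, unless they withdraw consent or answering would itself be harmful. Next to the reason, which is already recorded, note the date and the source of each stop (message, contact with a study member, other).

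The cost is two or three sentences and an amendment with ethics approval (8.2). Questionnaires, reminders and vouchers already exist, and safety handling and referral do not change. The downside is that a few distressed caregivers receive questionnaires, which they may decline, and some scores will stay missing. The change does not remove the message route that exists only in IND; it means that detection need not cost the T2 score.
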